## Abstract

**Background:**

Vitamin D plays an important role in human physiology and pathology. The receptor for vitamin D regulates 0.5–5% of the human genome. Accordingly, vitamin D insufficiency has been shown to increase the risk of several diseases. In recent years, based on growing evidence, on a role of vitamin D has been also postulated in reproductive health both in animals and humans, especially in female fertility female fertility. In vitro fertilization success was shown to be higher in women with appropriate reserves of vitamin D. However a causal relation has not been demonstrated and randomized controlled trials testing the effectiveness of vitamin D supplementation in IVF are warranted.

**Methods:**

This is a multicenter randomized double blinded placebo controlled study aimed at determining the benefits of vitamin D [25(OH)D] supplementation in improving clinical pregnancy rate in women undergoing IVF. Eligible women with a serum level of 25-hydroxyvitamin D [25(OH)D] < 30 ng/ml will be randomized. Recruited women will be given the drug (either 600,000 IU of 25(OH) D or placebo in a single oral administration) at the time of randomization. Two centres will participate and the sample size (700 women) is foreseen to be equally distributed between the two. Patients will be treated according to standard IVF protocols.

**Discussion:**

The primary aim of the study is the cumulative clinical pregnancy rate per oocyte retrieval. Clinical pregnancy is defined as the presence of at least one intrauterine gestational sac with viable foetus at first ultrasound assessment (3 weeks after a positive human chorionic gonadotropin [hCG] assessment). Secondary outcomes include: 1) clinical and embryological variables; 2) oocyte and endometrium quality at a molecular level. To investigate this latter aspect, samples of cumulus cells, follicular and endometrial fluids will be obtained from a subgroup of 50 age-matched good-prognosis cases and controls.

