### Interventions

#### Experimental design aim 1

Recruited women will be given the drug (either 600,000 IU of 25-OH-vitamin D or placebo in a single oral administration) at the time of randomization, thus 2–12 weeks prior to oocyte retrieval and managed according to a standardized clinical protocol of ovarian stimulation with in vitro fertilization (fresh cycle). Administration of the drug/placebo will be performed by the physician in order to guarantee a compete adherence to the protocol. No dose changes are foreseen. Patients will be asked to avoid further consumption of vitamin D after randomization.

Women whose cycle will be cancelled will not be excluded (intention to treat analysis). A specific software will establish the randomization list. Sun exposure during the study period will be recorded but it will not be a reason for drop-out. Serum 25-OH-Vitamin D will be reassessed at the time of hCG administration or, if the cycle will be cancelled, at the time of the decision to interrupt the treatment. The quantitative detection of total serum 25(OH) D levels will be performed using a commercially available kit based on a chemiluminescence technology (DiaSorin) with intra- and interassay coefficients of variations equal to 10 and 15%, respectively.

Patients will be treated according to standard IVF protocols as described elsewhere [12, 13]: since neither the clinicians nor the recruited women will be aware about vitamin D dosage, clinical management of ovarian stimulation will not be conditioned by the study.

In case of supernumerary oocytes or embryos deriving from the fresh cycle, the subsequent embryo transfer using thawed embryos or oocytes will be considered for the study outcome if performed within 4 months from oocyte retrieval and 25(OH) D serum levels will be reassessed.

Serum hCG assessment to detect pregnancy will be performed at + 14/+ 16 days after hCG administration. If positive, women will undergo a transvaginal sonography 3 weeks later.

Clinical pregnancy (primary outcome) is defined as the presence of at least one intrauterine gestational sac with viable foetus.

Dates of the study: 27/06/2016–26/06/2019

A schedule of enrolment, interventions and assessments of the study protocol is reported in Fig. 1.

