### Data collection and analysis

An electronic dataset will be filled (SPSS ver. 20, IBM).

All data will be recorded with paper case report forms and entered electronically at both participating sites using a common dataset. Original study forms will be stored in numerical order and stored in a secure and accessible place for 30 years after study completion. A biostatistician will perform quality control before data analysis, including check for double data entry and range for data values. Missing data will be included in the analysis using specific modern imputation methods.

Statistically significant differences will be determined using Fisher’s exact test, chi-squared test, Student’s t test or the Wilcoxon test, as appropriate.

An interim analysis (315 randomized completed cycles) of clinical pregnancy rates will be performed in order to highlight unforeseen or higher-than-expected effects of vitamin D supplementation. According to the Haybittle–Peto boundary rule, the statistical significance for deciding to stop the trial is set to *p*-value < 0.001 [18]. Results of the interim analysis will be available to all medical and laboratory staff. The steering committee decides on the continuation of the trial and will report to the involved ethics committees.

In accordance with national guidelines, the main outcome will be collected for every woman in order to complete their clinical charts. Since the main outcome is the clinical pregnancy rate as (defined as the presence of at least one intrauterine gestational sac with viable foetus), it has to be noted that its evaluation is highly standardized and fully objective. Moreover, according to legal requirements and standard clinical protocols, secondary outcomes related to the evolution of pregnancies will be easily collected through usual methods and reminders for contacting patients.

Given the study design, protocol adherence is foreseen to be complete. However, data will be analysed according to the “intention to treat” analysis.

Since the clinical trial is designed as minimal risk a formal committee for data monitoring is not foreseen.

Electronic monitoring of the datasets will be performed by two independent physicians every 3 months during recruitment focussing on: completeness of the data, eligibility criteria, date of randomization, treatment assignment, adverse events and endpoints, signed informed consent.

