### Sample size calculation

The sample size was calculated according to Kane [19] based on the following assumptions:

1) the primary outcome is the cumulative clinical pregnancy rate (CPR) per started cycle; 2) expected CPR in the deficient population 20% [7], 3) expected CPR in the supplemented population 30% [7], 4) expected proportion of women with insufficient serum vitamin D (< 30 ng/ml): 90% [20], 5) Type I and II errors of 0.05 and 0.20, respectively. Under these assumptions, a sample size of 300 randomized women per arm will allow us to detect with sufficient statistical power (*p* < 0.05) an absolute difference ≥ 10% in the CPR rate between the two groups using the chi-squared test.

Considering that 10% of recruited women are expected to have serum vitamin D levels ≥30 ng/ml (therefore they will not be randomized) and considering a dropout rate of 5%, it has been decided to recruit 700 women to reach the number of 600 required subjects. The full formula used for sample size calculation is provided as an additional figure (see Additional file 2).

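### The primary pregnancy rate is defined per oocyte retrieval in the abstract, but per started cycle and by intention to treat in the Methods; these denominators cannot all hold.

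*Protocol article*

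**What the plan says.** All references are to the protocol article.

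- **Abstract, Discussion paragraph.** "The primary aim of the study is the cumulative clinical pregnancy rate per oocyte retrieval". The denominator is women (or cycles) that reach retrieval.
- **Sample size calculation.** "the primary outcome is the cumulative clinical pregnancy rate (CPR) per started cycle". The 20% and 30% rates are listed under this definition, and the section then asks for 300 randomised women per arm.
- **Interventions, aim 1.** "Women whose cycle will be cancelled will not be excluded (intention to treat analysis"). Data collection and analysis repeats the principle: "data will be analysed according to the “intention to treat” analysis".
- **Interventions, aim 1, outcome definition.** "Clinical pregnancy (primary outcome) is defined as the presence of at least one intrauterine gestational sac with viable foetus". This fixes the event but gives no denominator. Transfers of thawed material from the same retrieval "will be considered for the study outcome if performed within 4 months from oocyte retrieval".

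Drug or placebo is given at randomisation, 2–12 weeks before retrieval. The rate of cancelled cycles is one of the variables that the trial compares between arms (Aim 2, and Experimental design aim 2).

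**The concern.** A single binary primary outcome needs a single denominator. Here the abstract removes women cancelled before retrieval and the Methods keep them. The outcome definition in the Methods does not settle the matter, because it describes only what counts as a pregnancy.

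The difference affects the randomised comparison. Reaching retrieval happens after randomisation and after dosing. The trial's own hypothesis is that vitamin D may change how many cycles are cancelled. If it does, the women who reach retrieval are a differently selected group in each arm, and comparing pregnancy rates among them no longer compares like with like. Two conflicting statements also leave room to choose the denominator once results are known.

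**Working it through.** **1. Reproduce the planned sample size.** Inputs from Sample size calculation: 20% v 30%, type I error 0.05, type II error 0.20, chi-squared test. The article does not state sidedness; I assume two-sided.

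n per arm = [1.960·√(2·0.25·0.75) + 0.842·√(0.20·0.80 + 0.30·0.70)]² / 0.10² = 293.2, rounded up to 294.

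This agrees with the stated 300 to within rounding. Power with 300 per arm is 80.9%. Recruitment also checks: 700 × 0.90 × 0.95 = 598.5, about 600. The sample-size arithmetic is not at fault.

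**2. Where a cancelled woman falls.** Take a woman who is randomised and dosed, starts stimulation and is cancelled before retrieval.

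| Statement | Is she in the denominator? |
|---|---|
| Abstract: per oocyte retrieval | No |
| Sample size: per started cycle | Yes |
| Interventions and Data collection: intention to treat | Yes |

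A woman who is randomised but never starts a cycle is kept only by intention to treat. Started cycles and all randomised women differ only by such women, and the article gives no separate count of them.

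**3. What the denominator does to a result.** The counts below are hypothetical, because the article gives no cancellation rate. The test is chi-squared without continuity correction.

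| Pregnancies, placebo v vitamin D | Denominators | Rates | Difference | p |
|---|---|---|---|---|
| 60 v 81 | 300 / 300 (all randomised) | 20.0% v 27.0% | 7.0 points | 0.043 |
| 60 v 81 | 270 / 270 (10% without retrieval in each arm) | 22.2% v 30.0% | 7.8 points | 0.040 |
| 60 v 81 | 270 / 285 (10% v 5% without retrieval) | 22.2% v 28.4% | 6.2 points | 0.094 |
| 60 v 78 | 300 / 300 (all randomised) | 20.0% v 26.0% | 6.0 points | 0.081 |
| 60 v 78 | 285 / 270 (5% v 10% without retrieval) | 21.1% v 28.9% | 7.8 points | 0.033 |

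With equal cancellation the rates and the difference shift, but the p-value hardly does (0.043 v 0.040). With unequal cancellation and a borderline result, significance can be lost or gained.

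**4. What it does to power.** If 20% and 30% are rates per started cycle, as the sample size section says, 300 per arm gives the 80.9% above. Suppose instead that they were per-retrieval rates and a share c of each arm had no retrieval (an assumption). The rates over all randomised women are then 0.20(1−c) and 0.30(1−c).

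| c | Rates over all randomised | Power, 300 per arm | n per arm for 80% |
|---|---|---|---|
| 3% | 19.4% v 29.1% | 79.3% | 306 |
| 5% | 19.0% v 28.5% | 78.2% | 314 |
| 10% | 18.0% v 27.0% | 75.3% | 337 |
| 20% | 16.0% v 24.0% | 68.9% | 392 |

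If all 700 × 0.90 = 630 randomised women were analysed (315 per arm), power at c = 10% would be 77.3%.

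**The case against.** The best defence is that the Methods are nearly consistent. The sample size section counts randomised women, the Interventions section expressly keeps cancelled cycles, and the analysis section repeats intention to treat. On that view one abstract sentence is the outlier and an analyst would follow the Methods. This stands as a guide to which statement should give way. It does not remove the contradiction, because the abstract's sentence purports to state the primary measure and the Methods' own outcome definition has no denominator to overrule it.

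Several stronger readings are tempting, and the article does not support them:

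- **A further denominator at the interim.** The article says "An interim analysis (315 randomized completed cycles) of clinical pregnancy rates will be performed". This reads naturally as the timing of that look and does not redefine the final outcome.
- **Dropouts handled inconsistently.** Inflating recruitment for 5% dropout while analysing by intention to treat is routine, and no sentence says that dropouts leave the analysis.
- **Pregnancies imputed to women without a transfer.** The article says "Missing data will be included in the analysis using specific modern imputation methods", but nowhere classes a woman without a transfer as missing, and it says that the main outcome will be collected for every woman. The scope of imputation is a detail that an article may leave to the analysis plan.
- **A reversed treatment effect.** One can construct a case in which vitamin D rescues half of a 10% cancellation share and the rescued women succeed 5% of the time. That gives 20.0% v 19.2% per retrieval and 18.0% v 18.25% per randomised woman. These differences are under one point and depend on chosen inputs, so they do not show that the conclusion would reverse.
- **An underpowered trial.** The lower power figures need 20% and 30% to be per-retrieval rates, which the sample size section does not say.

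**Conclusion.** The point holds as a contradiction in the primary outcome's denominator: per retrieval in the abstract, against started cycles and intention to treat in the Methods. It needs correcting because the per-retrieval version conditions on a post-randomisation event that the trial tests as an outcome. The likely numerical effect is modest. Reported rates and the difference change in any case; the test result changes materially only if cancellation differs between arms and the result is close to the threshold, and the examples of that rest on hypothetical counts. The planned sample size is sound on its stated basis. A reader might infer that the trial is underpowered or that its result could be reversed, but the article does not establish either.

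**What to change.** Replace the per-retrieval wording in the abstract and the per-started-cycle wording in Sample size calculation with one definition, and repeat it in Interventions and in Data collection and analysis. Suggested text:

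*The primary outcome is the proportion of all randomised women, analysed as allocated, who have at least one clinical pregnancy in the study cycle, from the fresh transfer or from a thawed transfer within 4 months of retrieval. Women whose cycle is cancelled, or who have no qualifying transfer, stay in the denominator as having no study-cycle pregnancy.*

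Two additions are needed:

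- State in advance, identically for both arms, how a natural conception before the cycle is counted. The article's main Discussion names better chances of natural conception as a potential benefit, so scoring every non-starter as a failure without comment could work against the active arm.
- Report per-started-cycle and per-retrieval rates as secondary results.

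Because women with no retrieval are classified directly, the window dated from retrieval does not have to be defined for them. The cost is wording, settled before unblinded outcome data are seen. The downside is that the reported rates will be slightly lower than per-retrieval rates.

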**Trial registration:**

The protocol was included in EudraCT on 22nd September 2015 with the registration number assigned ‘2015-004233-27’; it was submitted through the database of the Italian “Osservatorio Nazionale della Sperimentazione Clinica (OsSC)” - (National Monitoring Centre of Clinical Trials) to the National Competent Authority on 8th March 2016 and approved on 23rd June 2016.

## Background

Vitamin D plays an important role in human physiology and pathology. The activation of the vitamin D receptor (VDR) may regulate directly and/or indirectly the expression of a very large number of genes (0.5–5% of the total human genome). Accordingly, vitamin D insufficiency has been shown to increase the risk of several diseases including cancers, auto-immune diseases, infections and pregnancy complications [1, 2].

In recent years, a role of vitamin D has been also postulated in reproductive health. VDR is expressed in the ovary, the endometrium and the myometrium [3]. Moreover, vitamin D has been shown to influence female fertility potential in animals and humans [4, 5]. In vitro fertilization (IVF) success was demonstrated to be higher in women with appropriate reserves of vitamin D [6]. In a recent contribution from our group, we detected an adjusted odds ratio (a-OR) (adjusted for age, ethnicity, BMI, parity, duration of infertility, number of retrieved oocytes, number of transferred embryos, and study period) of 2.15 [95% confidence interval (CI): 1.23–3.77] for clinical pregnancy rate in women with vitamin D > 20 ng/ml compared to those with vitamin D < 20 ng/ml. A similar figure was observed when considering the implantation rate. Of note, this beneficial effect was even more evident when using a threshold of 30 ng/ml [7]. The large body of evidence available in animal models and data from in vitro studies in women strongly favour a causal relation, but evidence from RCTs is required to definitely support a role for vitamin D in influencing the chances of pregnancy. To date, only a small RCT has been published and no benefits emerged [8]. However, the study was insufficiently powered to draw definite conclusions (in total 117 women). Moreover, only women scheduled for frozen embryo transfer were included.

Exploring the mechanisms at the basis of the beneficial effects of vitamin D could also be relevant and may open new avenues of research. To date, there are few appealing findings but the scenario is incomplete, especially from interventional studies. Biological evidence from RCTs could conversely provide crucial insights on the role of vitamin D in influencing oocytes quality or endometrial receptivity.

Oocytes cannot be directly tested for molecular analyses. However, the evaluation of the cumulus and granulosa cells of the ovarian follicle could indirectly reveal the quality of the corresponding oocytes. The gene expression profile of cumulus-oocyte-complexes has been suggested to predict which embryos have the best chance of implanting in the uterus. In particular, the expression of COX20, BMP15 and GDF9 has been associated with the establishment of pregnancy or live birth. Other possible potential genes of interest but with less consistency among studies include GREM1, HAS2, VCAN, PTGS [9, 10].

Endometrial samples can conversely be obtained prior to initiate the IVF cycle and can thus be directly studied without interfering with the procedure. Of interest here is that the endometrium and the early pregnancy decidua also express VDR and could be other important targets of vitamin D. In a previous study from our group, vitamin D was shown to modulate the expression of genes important for embryo receptivity and to interact with the local cytokines in human endometrial cells [11].

In the present study the following hypotheses will be tested: 1) 25-hydroxyvitamin D [25(OH)D] deficiency negatively affects pregnancy rates in IVF cycles with an effect mediated through endometrial receptivity and/or oocyte embryo quality; 2) Vitamin D supplementation and restoration of adequate vitamin D levels may actually improve the prognosis of infertile women undergoing IVF procedures. The absolute magnitude of the benefit deemed to be clinically relevant in terms of cumulative clinical pregnancy rate is considered 10% (from 20 to 30%); 3) The molecular profiles of endometrium, follicular fluid and cumulus cells are modified in vitamin D-supplemented women with respect to molecules known to be associated with IVF outcomes and embryo implantation process.

## Methods

The study has been designed according to the CONSORT methodology.

### Aim

The present trial is aimed at determining the benefits of vitamin D supplementation in improving cumulative clinical pregnancy rate in women undergoing IVF. In particular, the three main aims of the study are as follows:
Aim 1: To determine the potential benefits of vitamin D supplementation in improving cumulative clinical pregnancy rate in women undergoing IVF.Aim 2: To investigate whether vitamin D supplementation might improve clinical and embryological variables such as: number of cancelled cycles, number of available oocytes, number of good quality embryos, units of FSH administered per retrieved oocyte, implantation rate of transferred embryos.Aim 3: To investigate the effect of vitamin D supplementation on oocyte and endometrium quality at a molecular level through a comparative analysis between treated and untreated patients based on the analysis of cumulus cells, follicular and endometrial fluids.

### Setting

This is a multicenter randomized superiority double blinded placebo controlled clinical trial with parallel groups and allocation 1:1.

Two Italian academic infertility units will be involved:
IRCCS Fondazione Ca’ Granda, Ospedale Maggiore Policlinico, Milan, Italy.IRCCS Ospedale San Raffaele, Milan, Italy.

### Participants

Inclusion criteria of women will be as follows: indication to IVF, age 18–39 years, less than 3 previous IVF attempts, body mass index (BMI) 18–25 kg/m^2^.

Exclusion criteria will be as follows: patients with anti-mullerian hormone serum level < 0.5 ng/ml, IVF cycle using frozen embryos/oocytes, vitamin D contraindications/side effects for consumption of vitamin D (high blood calcium levels or conditions that can lead to high calcium levels such as sarcoidosis, tuberculosis, parathyroid disease).

Eligible women will be informed on the study design and those agreeing to participate will sign an informed consent and will provide a blood sample for 25(OH) D assessment. Those with a serum level < 30 ng/ml will be randomized.

A CONSORT flow diagram of the study protocol is provided as an additional figure (see Additional file 1).

### Interventions

#### Experimental design aim 1

Recruited women will be given the drug (either 600,000 IU of 25-OH-vitamin D or placebo in a single oral administration) at the time of randomization, thus 2–12 weeks prior to oocyte retrieval and managed according to a standardized clinical protocol of ovarian stimulation with in vitro fertilization (fresh cycle). Administration of the drug/placebo will be performed by the physician in order to guarantee a compete adherence to the protocol. No dose changes are foreseen. Patients will be asked to avoid further consumption of vitamin D after randomization.

Women whose cycle will be cancelled will not be excluded (intention to treat analysis). A specific software will establish the randomization list. Sun exposure during the study period will be recorded but it will not be a reason for drop-out. Serum 25-OH-Vitamin D will be reassessed at the time of hCG administration or, if the cycle will be cancelled, at the time of the decision to interrupt the treatment. The quantitative detection of total serum 25(OH) D levels will be performed using a commercially available kit based on a chemiluminescence technology (DiaSorin) with intra- and interassay coefficients of variations equal to 10 and 15%, respectively.

Patients will be treated according to standard IVF protocols as described elsewhere [12, 13]: since neither the clinicians nor the recruited women will be aware about vitamin D dosage, clinical management of ovarian stimulation will not be conditioned by the study.

In case of supernumerary oocytes or embryos deriving from the fresh cycle, the subsequent embryo transfer using thawed embryos or oocytes will be considered for the study outcome if performed within 4 months from oocyte retrieval and 25(OH) D serum levels will be reassessed.

Serum hCG assessment to detect pregnancy will be performed at + 14/+ 16 days after hCG administration. If positive, women will undergo a transvaginal sonography 3 weeks later.

Clinical pregnancy (primary outcome) is defined as the presence of at least one intrauterine gestational sac with viable foetus.

Dates of the study: 27/06/2016–26/06/2019

A schedule of enrolment, interventions and assessments of the study protocol is reported in Fig. 1.

